**Reporting timeframe for SAEs and AEs:**

Investigators will promptly report unexpected adverse events, serious adverse events, unanticipated problems involving risk to subjects or others, and deviations to the IRB. Serious adverse events will be reported to the Tufts IRB within five business days. Non-serious adverse events will be reported to the Tufts IRB in a summary report, specifying the nature and frequency of the adverse events, at the time of continuing review. Any non-serious adverse events that are deemed an unanticipated problem will be reported to the IRB as for a serious adverse event. Unanticipated problems are defined as: 1) The nature, severity, or frequency is unexpected for the participant population or research activities; 2) related or possibly related to participation in the research; and 3) an event indicating that the research may place the participant or others at a greater risk of harm then was previously recognized.

The study physician will review all reports of AEs at least monthly. The study physician is the Medical Director of the inpatient Metabolic Research Unit at Tufts and has extensive experience in the safe conduct of human research procedures to protect human subjects. If adverse event monitoring suggests that events are occurring with greater frequency or severity than initially expected, the PI will submit a report of an Unanticipated Problem to the IRB, with an amendment if a modification of the study design is indicated.

In addition, all unanticipated problems involving risk to subjects or others, serious adverse events related to participation in the study and subject deaths related to participation in the study will be promptly reported by phone to the IRB.

**Accountability procedures as they relate to drugs, devices, and data:**

There are no drugs or devices in this study. Concerning computer files and data collection forms, these will use the subject ID and will not be linked to protected information. The computers used to enter or store study data will be password protected. All data will be entered into StudyTRAX. Security features of StudyTRAX targets include password protection, restricted access to users based on role in the study, role-based access to features, access audit trails, and hosting services (e.g., firewall, secure sockets layer). Taken together, these features ensure access control, audit control, data integrity, user authentication, and transmission security. The research project will be set up in StudyTRAX using their standard procedure which ensures exported datasets are de-identified as defined in the HIPAA privacy regulation [45 C.F.R. §164.514 (b)(2)].

1. **Subject Participation**
2. **Recruitment** A multi-staged screening process will be used to identify 12 suitable worksites for the study. We will contact worksites withign the greater Boston area including those which have previously expressed interest or with whom Tufts has corporate affiliations with to find 12 worksites who are eligible and interested in doing the study. The 12 shortlisted and eligible worksites, will be invited to enroll. Companies and government institutions in the professional sector, and located in the Greater Boston area who report 300 or more employees will be contacted by land mail and/or email with an initial information letter describing the study and highlighting the benefits of participation. Companies with greater than 900 employees will potentially be divided into 2 or more subunits to make up the 12 worksites. The initial information letter will invite interested worksites in applying to the intervention program. We will send follow-up information with further details of study participation to the companies who respond to the initial mailing. Study staff will meet in person or talk with HR personnel/company representative about the process of being considered for participation. HR personnel/company representative will then mail and/or email employees with the informational email and details about recruitment & screening day.
3. **Registration:** This study will be enrolled as a clinical trial on clintrials.gov.
4. **Screening Interview/Questionnaire:**

Those interested in participating will be screened on **Recruitment** Day. They will first be administered the screening ICF, and the screening will involve a questionnaire on exclusions and measurements of weight and height for calculation of BMI and the option to choose the diet or the HPI arm of the intervention. If the individual is eligible they will then be administered with the informed consent form (ICF) for baseline assessments. The **Recruitment** Days, screening and baseline measurements will be conducted by members of the Tufts team (study coordinators, research staff and investigators) depending on availability.

Randomization of worksites to the intervention or control condition will be done following the completion of baseline assessments. Once worksites are randomized to receive the intervention or weight-listed control condition, participants within the intervention worksite will be assigned to the intervention arm that they opted into at screening i.e. HPI or diet arm. However, those who had expressed an interest in the

iDiet will be further randomized to receive Yevo foods or a gift card. Once randomization has occurred, participants will be given the consent form to read and sign prior to enrollment in the study.

Any questions or concerns will be addressed by a study team member prior to signing of the ICF. Copies of the signed ICF will be given to the study participants. Enrollment of all participating sites and employees will occur over a 6 month period during the first year.

1. **Transportation:** No transportation will be provided for this study since all support and assessments are provided and conducted in the workplace.
2. **Informed consent process:** Eligibility for inclusion of a worksite is multistep and is summarized in the protocol (Section III, parts C and D).
   - 1. Informed Consent for Initial Web Survey For All Employees at Worksite
     2. HR Company Agreement Form
     3. Informed Consent for Worksite **Recruitment** Day and Screening
     4. Informed Consent for Baseline Assessments For All Employees who have expressed an interest to join an intervention group at Worksite
     5. Informed Consent for:
3. iDiet Intervention
4. Human Performance Institute Intervention
5. Control group

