2. **Experimental design:** 18-month worksite randomized controlled trial, in which worksites are randomized to receive the multiple intervention wellness programs or the control program. Control participants will participate in outcomes assessments only for the first 6 months, after which they will enroll in the intervention of their choosing. Both arms (HPI and the iDiet) will receive direct training from the coaches who deliver these commercial programs at their respective worksite and/or via a concurrent online session, or at an alternative commutable location that is offsite in the case of the HPI program. A total of 400 participants in the worksites allocated to the intervention, with approximately 20 participants in the HPI arm and 30 in the iDiet arm per worksite is planned to ensure even balance in each of the study arms. If more than 20 individuals are interested in and eligible for the HPI arm or more than 30 are interested in and eligible for the diet arm, participants will be enrolled into the study on a first-come, first-serve basis, including a small upward or downward adjustment in the total number of employees enrolled per site to ensure that the overall targeted number of participants is achieved. All participating individuals, from both the intervention wellness and control programs, can opt-in to either the HPI or the iDiet weight loss program. However, if they choose to participate in the weight loss intervention they will then be randomized into one of two groups: iDiet with food provided or iDiet with a gift card,. The study flow and primary intervention groups are described below:

**
[figure not shown]
**

*^1^The number of controls reflects study design in which sign up for the intervention and distribution of the intervention sites happens before baseline to ensure equivocal disposition*.

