The increase in vitality score in the intervention worksites compared to controls is expected to be 9 points at both time points compared to the control. Since randomization is at the worksite level, the total variance includes both the within worksite and between worksite variance. Based on a within worksite standard deviation of 15 and 20 people per worksite and a between worksite standard deviation of at most 3.4, 12 worksites with a 2:1 worksite allocation in favor of treatment are needed to have 80% power to detect an expected increase in vitality score of 9 points.

For the participants electing to participate in the behavioral weight loss program, randomization to either with provided Yevo foods or a gift card such that one half of the participants are in one group and the other half will be assigned to the remaining arm.. Assuming worksite is a fixed variable, 8 worksites with 30 subjects each (240 total subjects) is at least 80% powered to detect a 2.4% difference in weight loss with provided food compared to gift cards assuming no diet by food interaction. If there is a significant food by diet interaction, the study will have an 80% power to detect an interaction that is a 4.5% difference in weight change with provided food for iDiet and 3% improvement in diet.

Data analyses will be performed using the latest version of SAS for Windows, currently 9.4 (Cary, NC: SAS Institute Inc.). All testing will be two-sided and results will be judged statistically significant if the observed significance level (P value) is <0.05. Data will be examined graphically and numerically for outliers and other aberrations that might lead to misleading results. Data may be transformed prior to formal analysis if necessary to fit the assumptions for the statistical model to be employed. Both studies (HPI intervention and the iDiet intervention) will be analyzed according to Intention-To-Treat principles to best reflect what happens when individuals start one of the interventions. If necessary, missing data will be estimated using multiple imputations using the MI Procedure of SAS for Windows.

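### The study consent is signed only after allocation is known, so employees already measured at baseline can refuse depending on their arm, and the protocol does not say they stay in the analysis

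*Protocol*

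**What the plan says.** The Protocol's Screening Interview/Questionnaire section gives a sequence.

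- On Recruitment Day: "They will first be administered the screening ICF". The employee also chooses the diet or the HPI arm.
- Next: "If the individual is eligible they will then be administered with the informed consent form (ICF) for baseline assessments".
- Then: "Randomization of worksites to the intervention or control condition will be done following the completion of baseline assessments".
- After that, "participants within the intervention worksite will be assigned to the intervention arm that they opted into at screening i.e. HPI or diet arm", and those who chose iDiet are randomised to Yevo foods or a gift card.
- Last: "Once randomization has occurred, participants will be given the consent form to read and sign prior to enrollment in the study".

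The list under Informed consent process matches this. A form for baseline assessments is followed by three group-specific forms: iDiet, HPI and control.

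Three other places bear on the point.

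- Sample size and statistical analyses speaks of enrolling up to 700 people so that 600 complete baseline and are randomised. Enrolment there precedes randomisation.
- The footnote to the study-flow figure under Experimental design says that "sign up for the intervention and distribution of the intervention sites happens before baseline to ensure equivocal disposition".
- The analysis text says that both studies will be "analyzed according to Intention-To-Treat principles to best reflect what happens when individuals start one of the interventions".

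**The concern.** Employees cannot be blinded to whether they receive a free programme now or wait six months. If the form that admits them to the study comes after they know this, those who refuse at intervention sites may differ from those who refuse at control sites. A control may lose interest on learning of the wait. An HPI employee may find that the 2.5-day workshop does not suit. An iDiet employee may have wanted the other of food or gift card. Both primary comparisons are therefore exposed: vitality in HPI against controls, and weight under provided food against gift card.

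A person who has not agreed to follow-up supplies no six-month outcome, and analysis cannot create one. The protocol does not say whether a baseline completer who refuses the later form remains in the analysis set. The only gloss on ITT speaks of people starting an intervention. Controls start nothing in the first six months, and the gloss gives no rule for people randomised who never start.

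**Working it through.** **1. Order of events, section by section**

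| Place in the protocol | Enrolment | Site allocation |
|---|---|---|
| Screening Interview/Questionnaire | after randomisation, on signing the last form | after baseline |
| Sample size and statistical analyses | before baseline and randomisation | after baseline |
| Footnote to the study-flow figure | sign-up before baseline | before baseline, if taken literally |

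The first two rows disagree on enrolment. The third disagrees with both on allocation. If the footnote were followed, self-reported baseline vitality, which is a model covariate, would be collected with allocation known.

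**2. What is fixed before allocation.** Screening consent, programme choice, baseline consent and baseline measurements are all complete. The HPI analysis compares people randomised to intervention with control-site employees who chose HPI beforehand. Programme choice is thus protected. Staying in the study after allocation is not.

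**3. The plan's own power figure.** Inputs from Sample size and statistical analyses: within-site SD 15, 20 people per site, between-site SD at most 3.4, 8 against 4 sites, difference 9 points, two-sided 0.05.

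- Variance of a site mean = 3.4² + 15²/20 = 11.56 + 11.25 = 22.81
- SE of the difference = √(22.81 × (1/8 + 1/4)) = 2.925
- Noncentrality = 9/2.925 = 3.077
- Power, noncentral t with 10 df = 79.2%

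This reproduces the stated 80%. There is no arithmetic error behind this point.

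**4. Illustrative loss of precision.** The protocol gives no refusal rate, so the rates here are assumed.

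| Refusal in both arms (assumed) | People per site | SE | Power |
|---|---|---|---|
| 10% | 18 | 3.004 | 77.0% |
| 20% | 16 | 3.100 | 74.4% |
| 30% | 14 | 3.219 | 71.3% |

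**5. Illustrative bias.** Suppose a share q of one arm refuses, nobody in the other arm does, and refusers' mean change differs from signers' by D points. The signers' mean then departs from the mean of the whole arm by q × D. Both q and D are assumed. The type I error uses the no-loss SE of 2.925.

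| q | D | Bias (points) | Share of 9 points | Type I error |
|---|---|---|---|---|
| 5% | 5 | 0.25 | 3% | 5.1% |
| 10% | 9 | 0.9 | 10% | 5.9% |
| 20% | 9 | 1.8 | 20% | 8.6% |
| 30% | 15 | 4.5 | 50% | 28.6% |

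The sign is unknown. With refusal in both arms and the same D in each, q becomes the difference in refusal between arms. The width of this range shows that the protocol does not determine the size.

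**The case against.** The strongest reply is that participants are already identified, consented to screening and baseline, measured, and committed to a programme before allocation. What remains is attrition with a known denominator and baseline data. That is correct, and it limits the point. A reader might infer from the late consent that the compared groups are chosen after randomisation. The documents do not support that, because the HPI comparator is defined by choice made before randomisation and the sample-size text counts baseline completers as those randomised.

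A reader might also infer that ITT is restricted to people who start. The protocol commits to ITT principles, and the remark about starting is a reason given for that commitment, not a definition of the population. It could not define the control set in any case. The exact analysis set may be in the analysis plan, which the protocol promises before enrolment and which is not shown. The texts of the consent forms are also not shown, so what refusal entails cannot be confirmed.

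The model adjusts for baseline vitality, weight, ethnicity and gender, and multiple imputation is available. These address selection on measured factors, but not on unmeasured motivation. Employer agreement and weekend sessions should reduce refusal of the workshop. Data from people who withdraw are kept, but the stated reason is CONSORT reporting, which does not settle whether they are analysed. Finally, the footnote is garbled and its figure is not shown, so it is better read as an inconsistency to correct than as evidence that baseline is taken with allocation known.

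One part of the concern survives all of this. The order of consent is set in the protocol, and no analysis plan can recover outcomes from people who have not agreed to follow-up.

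**Conclusion.** The point holds as a risk of differential loss after randomisation, created by the stated consent order, together with an unresolved conflict over when enrolment and allocation occur. It does not show that the plan selects its groups after randomisation, and it is not a power error. The bias cannot be derived from the protocol. Under the assumed values above it runs from 0.25 to 4.5 vitality points with unknown sign, and any figure within that range rests on assumption alone. The same mechanism applies to food against gift card, again with no figure available. The case for change rests on how cheaply the route can be closed, not on a demonstrated bias.

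**What to change.** - At or before baseline, and before worksites are randomised, obtain one consent covering all follow-up assessments under either allocation. Keep the later iDiet, HPI and control forms as permission for programme participation only.
- State that every baseline completer in a randomised worksite is analysed by worksite allocation, by programme choice made before randomisation and, for iDiet, by assigned food or gift-card group, whether or not they start. Replace the remark about starting.
- Report refusals after allocation by arm.
- Bring the figure footnote, the sample-size section and the Screening Interview/Questionnaire section to one order: sign-up and baseline, then randomisation.

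The cost is a consent amendment with ethics review and the follow-up of some people who never start. No extra participants are needed. If enrolment has finished, the analysis rule and the reporting of refusals can still be adopted.

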**Confidentiality:** Upon entry into the study, a coded study ID will be assigned to the study participants and also for questionnaires to maintain confidentiality within the research setting. The signed consent forms and any paper data collection forms will be transported from the study site in a locked briefcase and will be kept in a locked file cabinet at the USDA Human Nutrition Research Center. Only the principal investigators and Tufts Study Coordinator will have access to the master code linking subject identifiers and their study ID. The other study team members will have restricted or limited access to components of the data that are essential for intervention delivery or will only have access to de-identified data. Participants will also have access to their own weight data (iDiet) and all biometric data (HPI) and are encouraged to share it with their wellness coaches as they see fit. The master file with study ID code will be destroyed 10 years after the study is complete. Signed consent forms and screening questionnaires that are collected at study sites will be kept in a number lock briefcase at collection sites and during transport back to Tufts University. Only the principal investigators and Tufts study coordinator will have access to unlock the file cabinet. The Tufts Study Coordinator will keep the key for the file cabinet. After 10 years all hard copy data will be shredded. Additionally, data will be kept in a secured protected drive at Tufts for 10 years after closure of the study unless the IRB grants longer. All investigators at Tufts undergo the required continuing recertification for ethical research by human subjects. Computer files and data collection forms will use the subject ID and will not be linked to protected information. The computers used to enter or store study data will be password protected. All data will be entered into StudyTRAX. Security features of StudyTRAX targets include password protection, restricted access to users based on role in the study, role-based access to features, access audit trails, and hosting services (e.g., firewall, secure sockets layer). StudyTrax uses the data center services at Rackspace, a premier hosting company. Characteristics of the Rackspace data center include a secure biometric access that is monitored 24/7 by closed circuit cameras; no public access; large-scale HVAC systems; continuous uninterrupted power supply systems; diesel engine backup on site and enterprise class routing equipment. In addition, there is a dedicated managed Cisco router firewall; all server requests are transmitted over SSL using 256-bit encryption; redundant array of independent disks (RAID) level 5, nightly system; database backups and nightly database integrity checks. StudyTrax database will not include computer IP addresses. StudyTrax will be notified that investigators are done with the data and have finished the study. At that time, StudyTrax will delete all participant data and audit logs. Taken together, these features ensure access control, audit control, data integrity, user authentication, and transmission security. The research project will be set up in StudyTRAX using their standard procedure which ensures exported datasets are de-identified as defined in the HIPAA privacy regulation [45 C.F.R. §164.514 (b)(2)].

1. **Collaboration:** This project is collaboration between researchers at the JM USDA HNRCA at Tufts University, Johnson and Johnson’s Wellness and Prevention Division (J&J WPN), and Yevo International, LLC (Yevo Intl).

For those employees participating in the HPI program, their first and last name as well as their work email address will be provided to J&J-WPN identified, Performance Programs Inc. (a third party provider) that will disseminate a package of information, and a small battery of questionnaires directly to the participant. This data will be returned to J&J’s WPN coaches and will be used during the 2.5 day workshop. Similarly, participants’ information such as first and last names and email address will have to be shared with iDiet so these commercial programs can be effectively communicated and disseminated to the participants.

Most study data is being entered in a secure website which will store the data under encrypted numbers. Only summary report data will be shared with our collaborating investigators at J&J WPN and Yevo Intl. However, no data files or datasheets with identifiers will be transacted or shared between Tufts University and J&J WPN (except participants may share their own data with the professional coaches for feedback) or Yevo Intl. Companies will not be providing information for this study. All outcome measures required for the study will be obtained by Tufts. Should we identify any information that would be useful and can be provided by the companies we will request and obtain IRB permission prior to transfer and use of such information.

For reports, presentations and such activities aggregate data will be provided or shared with no reference to any identifiers.

1. **Alternatives:** The alternative to participating in this study is not to participate. Additionally, since these are commercial programs, another alternative is to participate in these programs on their own time.
2. **How new information will be conveyed to the study participant and how it will be documented:** Participants will be informed in writing of any significant new findings developed during the course of participation in this research that may have a bearing on their willingness to continue in this study. We will provide each participant with a summary of trial results after the primary paper for the study is published.
3. **Payment, including a prorated plan for payment**

Participants will receive up to $75 over the course of the study, for completing the assessments outlined at each time point (Table 1). Participants will receive this amount as $25 for doing all 6 month testing, $25 for doing all of month 12 testing, and $25 for doing all of month 18 testing. These amounts will be prorated and given to participants based on completion of testing at each time point and if participants withdraw, or are withdrawn from the study for any reason. If institutional policy dictates that employees are not allowed to receive such stipends then such policies will override the provision of stipends as stipulated for each time point.

For diet intervention participants randomized to the voucher group, vouchers of $63 will be given at baseline and weeks 4, 8, 12, and 16, 20 the time of food distribution, for a total of $378 in gift card vouchers.

1. **Payment for research-related injury:** Subjects will be encouraged to see their primary care physician, however no monetary compensation for injury will be offered.
2. **Outcomes**

The primary outcomes are a change in measured weight from baseline to 18 months in iDiet participants, and a statistically significant improvement in energy status for HPI participants and baseline to 6 months in comparisons with the controls. Additional outcomes include: cardiometabolic risk factors, quality of life, employee productivity, purpose in life, measured dietary intake and cravings, satiation and satisfaction of food provisions, as well as changes in physical activity. Further outcomes include changes in weight, blood pressure employee energy and productivity in non-participating employees at the intervention worksites. Differences in overall mean values between the intervention participants and controls, as well as overall mean values between interventions will be compared using *t*-tests and proportions will be compared using *χ*2 analyses.

1. **Tissue banking considerations:** There will be no tissue samples taken as part of this study and no tissue banking is planned or anticipated.

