The proposed research will implement a randomized controlled trial of two very different worksite wellness programs aimed at promoting wellness and health related quality of life, one with a particular focus on improvements in reported energy levels and the other focused on weight control. The project brings together our expertise in worksite nutrition studies, community weight loss programs and high quality health outcomes. The programs being tested differ in emphasis, approach and delivery, of the health-related wellness they recommend, and by combining them worksites potentially can reach a broader audience than if only one program was offered. The HPI program focuses on energy management and uses the sciences of performance psychology, exercise physiology and nutrition, while the iDiet weight management program emphasizes specific dietary composition goals based on recent promising weight control research by us and others (36-40) and will include an arm with provided foods. Additionally, the study will also examine whether there is a “ripple effect” of the benefits of the interventions from the worksite participants on their co-workers. This latter novel component of our study is based on research by us and others (18, 26, 27, 36, 38) suggesting that successful weight control interventions benefit both the direct participants and the household members who live with them and/or their work colleagues. For example, in a recent study by our team, weight changes were -1.3 ± 0.7kg, respectively (p=0.03) for individuals associated with individuals participating in an intervention versus the individuals associated with wait-listed controls (36). The likely explanation for this effect is that shared meals and exercise habits lead to favorable changes in energy balance in the non-participating adults, an effect that is also anticipated in worksites and, if proven here, could provide a new approach to helping resolve the obesity epidemic in worksite personnel themselves.

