**Summary of eligibility requirements for worksites to participate**

1. 300 or more employees from a for-profit or non-profit company and/or government institution (including schools, government agencies).
2. Available address and/or email contact for HR/company representative.
3. After understanding the study purpose, HR/company representative and administration’s willingness to be randomized to control or intervention group, and to host onsite and/or online iDiet weight loss groups and facilitate the implementation of the HPI workshop including allowing the interested employees to participate on the assigned dates.
4. Does not have an active weight loss/wellness intervention program onsite currently or within past 6 months or a pending contract for implementation in the immediate future (defined as weekly behavioral groups run by an outside commercial company for ≥14 weeks per year).
5. Low employee turnover rate (approximately 15%)
6. Company has been in operation for at least 3 years
7. HR/company representative can provide the Tufts team with aggregate demographic information (age range of employees, number of males and females etc.).
8. HR/company representative is willing to sign a consent form agreeing to company participation; also, HR/company representative is willing to complete questionnaire to allow preliminary assessment of eligibility, and then send around information and request employees to complete screening questionnaire (or provide emails to Tufts team to do this).
9. HR/company representative is supportive of the study, anticipating that employee enrollment in the program arms will not be problematic (approximately 50 total employees), and are able post informational flyers and study information for employees around the worksite and send occasional reminder emails to all employees prior to the two health surveys (or provide emails to Tufts team so that they can make these contacts).
10. There is a room available for the Tufts team to lead seminars and groups at times that are convenient to the worksite. Also, a bulletin board available for study flyers, and central location for distribution of study handouts and setting up periodic booth for information.
11. **Subject Characteristics**
    - 1. Inclusion criteria:
         1. Willingness to sign an informed consent form
         2. ≥ 21 years of age

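### The co-worker spillover outcome is defined only at intervention worksites, so it lacks the control-site comparison that its stated aim needs

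*Protocol*

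**What the plan says.** The Background of the protocol states that "the study will also examine whether there is a “ripple effect” of the benefits of the interventions from the worksite participants on their co-workers". It describes the effect as "an effect that is also anticipated in worksites and, if proven here, could provide a new approach" to obesity in worksite personnel. The supporting evidence is the team's earlier study, which reported a weight change of -1.3 ± 0.7 kg (p=0.03) "for individuals associated with individuals participating in an intervention versus the individuals associated with wait-listed controls".

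The Outcomes section lists, after the primary and additional outcomes, further outcomes: "changes in weight, blood pressure employee energy and productivity in non-participating employees at the intervention worksites". The sentence that follows names two sets of comparisons: intervention participants against controls, and one intervention against another. Non-participants appear in neither.

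Two other places touch on employees who do not enrol. The worksite eligibility list requires the company to "send occasional reminder emails to all employees prior to the two health surveys" (or to supply addresses so that the study team can do so). The list of consent forms under Informed consent process begins with "Informed Consent for Initial Web Survey For All Employees at Worksite".

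**The concern.** Spillover is a causal claim: co-workers change because colleagues took part. A change measured only at intervention sites also contains seasonal and secular drift, regression to the mean, unrelated workplace changes, and any shift in who answers the second time. Randomising worksites is what would separate these, and the trial does randomise worksites. If the outcome is analysed as defined, a fall in co-workers' weight could be reported as a ripple effect when employees at the control sites changed just as much. The reverse could also happen, with a real effect hidden by an upward drift.

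**Working it through.** The protocol gives no sample size, power or effect size for this outcome, so it has no figure of its own to reproduce. The check is mainly a reading of the sections against one another.

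**Sections side by side**

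- *Aim (Background):* an effect on co-workers, possibly to be proven in this trial.
- *Precedent (Background):* a contrast with associates of wait-listed controls.
- *Outcome (Outcomes):* non-participants at intervention worksites only.
- *Stated comparisons (Outcomes):* participants with controls, and intervention with intervention.
- *Who the controls are (Experimental design; Tables 1 and 2):* people at control sites who have enrolled, are assessed for 6 months and then start a programme. They volunteered for a programme, so they cannot stand in for employees who did not.
- *Available randomised comparator (Sample size and statistical analyses):* 4 control worksites against 8 intervention worksites.
- *Measurement (Tables 1 and 2):* weight, blood pressure and questionnaires are scheduled for enrolled HPI and iDiet groups and their future counterparts. There is no column for non-participants in either arm.

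The aim and the precedent need a control group. The outcome definition leaves it out, and no visible section puts it back.

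**Illustration of the mechanism (all SDs, drifts and numbers per site are assumptions)**

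Let the variance of a site-mean weight change be v = SD_between² + SD_within²/m, with m non-participants measured per site.

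- Before-after at 8 sites: SE = √(v/8), t-test with 7 df.
- Controlled, 8 versus 4 sites: SE = √(v(1/8 + 1/4)), t-test with 10 df.

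Worked case: SD_within 4 kg, SD_between 0.5 kg, m = 20.

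- v = 0.25 + 16/20 = 1.05.
- Before-after SE = √(1.05/8) = 0.36 kg. With no spillover and a common drift of 0.5 kg, the noncentrality is 0.5/0.36 = 1.38, and the test is significant 22% of the time.
- Controlled SE = √(1.05 × 0.375) = 0.63 kg. A drift common to both arms cancels, and the type I error stays at 5%. Power for a 1.3 kg difference is 46%.

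Over SD_within 3 to 5 kg, SD_between 0.25 to 0.5 kg and m = 20 to 50:

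| Common drift, no spillover | Before-after result significant |
|---|---|
| 0 kg | 5% |
| 0.3 kg | 9–32% |
| 0.5 kg | 17–69% |
| 1.0 kg | 51–99.8% |

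Power of the controlled contrast for 1.3 kg over the same grid is 35–97%. Whatever v is, the ratio of the two standard errors is √(0.375/0.125) = √3 = 1.73.

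The table shows how the problem works. It does not estimate its size in this trial.

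**The case against.** The best defence is that an outcome list names measures and people, not contrasts. The protocol prescribes no before-after test for non-participants and promises a formal data analysis plan, which is not at hand. A low-ranking outcome is commonly left to such a plan. The spillover aim is also absent from the numbered technical objectives, and the outcome ranks as a further one.

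The point about rank stands and limits the importance of the finding. The appeal to an analysis plan does not remove it: the restriction to intervention worksites is in the protocol's own definition, and a plan that followed it would have no comparator.

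A reader might be tempted to go further in four ways that the documents do not support.

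- *The trial can neither prove nor refute spillover.* This is too strong. The design contains control sites and could support a controlled version.
- *Blood pressure in non-participants has no data at all, and a survey is the only contact with them.* Some text after the list of consent forms is not in the public copy. What can be said is that no visible section schedules these measurements.
- *The surveys already collect self-reported weight at control sites at suitable times.* Neither the content nor the timing of the surveys is stated. Nor is it stated that the initial web survey is one of the two health surveys.
- *The bias is 23–77% of the expected effect.* That follows from assuming a drift of 0.3 to 1.0 kg and dividing by 1.3 kg (0.3/1.3 = 23%; 1.0/1.3 = 77%). The documents give no drift.

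**Conclusion.** The point holds as a mismatch between a stated aim and the population in which its outcome is defined. As written, the outcome has no concurrent comparator and cannot distinguish spillover from common drift or from changes in who responds. The direction and size of the resulting bias are unknown from the documents. Nothing in the HPI or iDiet primary analyses depends on this outcome, so the primary conclusions stand. The change is worth making because the Background treats the effect as something the trial might prove, and because the randomised control sites needed for it are already in the design. The conclusion rests on the visible text of the protocol.

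**What to change.** In Outcomes, define this outcome as the change in non-participating employees at intervention versus control worksites from baseline to month 6, before control sites start a programme. Analyse it with worksite as a random factor, as the protocol already does for the HPI comparison. Fix non-participant status at sign-up, which precedes worksite randomisation, so that the two groups are comparable.

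Use the two all-employee health surveys, which every worksite must support as a condition of eligibility, provided the sponsor confirms that they ask for the relevant measures and that the second is completed by month 6. For weight and blood pressure, either state how they are obtained in non-participants or limit the outcome to what the surveys collect.

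If the surveys fit, the cost is a change of wording and one more mixed model. If they do not, new questions or a new survey date, with the matching consent, would be needed. In either case the 8 versus 4 contrast is less precise than the before-after change, by the factor of 1.73 shown above under equal site variance, and it may be inconclusive.
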